**Table 1 Tab1:**
[figure not shown]
Ecological momentary assessment items

### Distal outcomes

#### Patient Health Questionnaire (PHQ-9)

The PHQ-9 [29] is a self-report questionnaire aimed at using nine items to measure the nine DSM criteria for depression. The items are scored on a 4-point Likert scale ranging from never (0) to very often (3). A minimum score of 0 and a maximum score of 27 can be obtained on the PHQ-9, with a higher score indicating more depressive symptoms. The PHQ-9 is designed and validated to detect and monitor depression [30].

#### Mental Health Continuum-Short Form (MHC-SF)

The MHC-SF [31] is a 14-item questionnaire aimed at measuring positive mental health. These items measure emotional well-being (3 items), social well-being (5 items), and psychological well-being (6 items) and are scored on a 6-point scale ranging from never (0) to every day (5). An average can be calculated on the MHC-SF, with a higher average score indicating greater well-being.

#### Questionnaire about the process of recovery (QPR)

The QPR [32] is a questionnaire aimed at measuring personal recovery with 15 items. These items (e.g., “I feel better about myself” or “I can actively engage with life”) are scored on a 5-point Likert scale ranging from disagree strongly (0) to agree strongly (4). A minimum score of 0 and a maximum score of 60 can be obtained on the QPR, with a higher score indicating greater personal recovery.

#### EuroQol-5 Dimension (EQ-5D)

The EQ-5D [33] is a self-report questionnaire designed to measure health-related quality of life across five key dimensions: mobility, self-care, usual activities, pain/discomfort, and anxiety/depression. Each of the five dimensions is rated on 5 levels of severity, with responses ranging from “no problems” to “severe problems.” The EQ-5D also includes a visual analog scale (VAS), where individuals rate their overall health on a scale from 0 (worst imaginable health) to 100 (best imaginable health).

### Procedure

The study was approved by the Medical Ethics Review Committee (NL87481.091.24), and is registered in the Dutch Trial Register (NL-OMON57144). Written informed consent will be obtained by a member of the research team before any study procedures start.

Participants will be enrolled by the research team in collaboration with the treating clinicians.

#### Design phase

The participants (patients and therapists) will attend two online focus group interviews (60 min each) to discuss the design of JITAIs for behavioral activation in depression using a topic list with prompted questions. After the focus groups, a template for the intervention message will be developed in m-Path and tested by two patients and two therapists for 2 weeks, followed by individual interviews regarding their experiences. Based on their experiences, a final version will be developed and examined during the evaluation phase. Patients will receive a remuneration of 25 euros after completing the focus group interviews.

#### Evaluation phase

The participants in the TAU + JITAI group first receive instructions on installing m-path [34] on their phones. Table 2 provides an overview of the measures and assessment times.

**Table 2 Tab2:** Overview of the measures and assessment times for patients in the TAU + JITAI and TAU groups

	Baseline (week #)	Evaluation (week #)					
	1	1	2	3	4	5	6
Measures							
CSQ-8							•
SUS							•
TWEETS							•
EMA survey	•	•	•	•	•	•	•
PHQ-9	• +	• +					• +
MHC-SF	• +	• +					• +
QPR	• +	• +					• +
EQ-5D	• +	• +					• +

*CSQ-8* Client Satisfaction Questionnaire, *SUS* System Usability Scale, *TWEETS* Twente Engagement with Ehealth Technologies Scale, *EMA survey* Ecological Momentary Assessment survey, *PHQ-9* Patient Health Questionnaire-9, *MHC-SF* Mental Health Continuum-Short Form, *QPR* Questionnaire about the process of recovery, *EQ-5D* EuroQol-5 Dimension

• = TAU + JITAI assessment

+ = TAU only assessments

They will complete baseline questionnaires (PHQ-9, MHC-SF, QPR, and EQ-5D) and undergo a 1-week baseline period with two EMA surveys per day following a semi-random sampling in time blocks of 1 h (e.g., 09:00–10:00; 12:00–13:00; 15:00–16:00, and 18:00–19:00). Each assessment takes place at random moments in one of the time blocks, and scheduling of the time blocks is decided by the participants at the start of the baseline. After the baseline period, the intervention phase (MRT) will start and last 6 weeks. During the MRT, participants receive four EMA surveys per day—following semi-random sampling in time blocks of 1 h—which serve as a decision point. At each decision point, the participant is eligible for randomization if they (1) completed the EMA and (2) met a prespecified tailoring-variable threshold indicating that they are in the symptomatic half of the item scale (i.e., a vulnerability state for withdrawal/avoidance). Because the EMA includes both negatively and positively valenced items, thresholds are operationalized in a directionally consistent way: for negatively valenced symptom items (e.g., “I feel down,” “I feel tired,” “I feel listless”), eligibility is defined as a score ≥ 4; for positively valenced functioning items (e.g., “I feel energetic”), eligibility is defined as a score ≤ 4. This threshold was selected to identify "moderate-or-worse" vulnerability states where the risk of avoidance is elevated [35] while managing participant burden by preventing prompting during mild or asymptomatic states. If the decision point is eligible for randomization, there is a 50% probability of receiving a JITAI and a 50% probability of receiving no JITAI. Thus, randomization occurs repeatedly within participants across eligible decision points. Allocation to the TAU + JITAI and TAU groups is not randomized. Within the TAU + JITAI condition, randomization at eligible decision points is generated automatically by m-path (simple randomization), and recruiters do not have access to future assignments. Because of the nature of the intervention, participants, therapists, and researchers are not blinded to study condition; therefore, no formal blinding or unblinding procedures apply.

For each participant, the tailoring variables will represent (1) one of the EMA items assessing depressive symptoms that exhibited the highest average score during their baseline period, and (2) one of the EMA items assessing depressive symptoms that the participant rated as “most impactful” on their daily functioning identified via a shared decision-making procedure following the baseline week. Specifically, a researcher and the participant jointly review visualized baseline EMA data (e.g., timeline plots of the symptom items), and the participant identifies which symptom most hindered their daily functioning and/or engagement in planned activities. This self-identified symptom is operationalized as the “impactful” tailoring variable. At the end of each study day, participants will receive an EMA survey that does not serve as a decision point. Two questions are added to the evening survey (activity level and best moment of the day). Importantly, the JITAIs are embedded in a therapist-supported treatment. During weekly therapy sessions, the EMA data collected during the week are visualized (e.g., timeline plots of mood and activities) and reviewed collaboratively by the therapist and participant. This integration aims to support engagement. The questionnaires completed at baseline (PHQ-9, MHC-SF, QPR, and EQ-5D) will be administered again at the start of the JITAI phase and at the end of treatment. In addition, at the end of treatment, participants will complete questionnaires regarding the acceptance of the JITAIs (CSQ-8, SUS, TWEETS). Participants in the TAU group will complete these questionnaires (PHQ-9, MHC-SF, QPR, EQ-5D) at the same time points. Participating patients in the TAU + JITAI group will receive a remuneration of 25 euros when they have completed the questionnaires at the last time point. Therapists will be interviewed at the end of treatment to share their experiences with patients using JITAIs.

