### Proximal outcomes

#### Ecological Momentary Assessment (EMA) survey

A total of 16 questions are included in the EMA questionnaire (see Table 1). The morning questionnaire begins with an assessment of rest (I feel rested) rated on a scale ranging from not at all (1) to very much (7). Four items assessing depressive symptoms, which are based on the PHQ-9, are related to mood and energy level (i.e., “I feel down”; “I feel tired”; “I feel listless”; “I feel energetic”) and two items concerning well-being (“I feel satisfied”; “I feel cheerful”) [27]. These mood and well-being items are also rated on a scale ranging from not at all (1) to very much (7). These momentary mood and energy items also serve as tailoring variables at decision points during the MRT. Importantly, these tailoring variables indicate vulnerability or opportunity states in which withdrawal or avoidance is more likely and external prompting may facilitate the start of a feasible activity, consistent with an activation-first behavioral activation model. Additionally, participants are asked about their current location (e.g., at home, at school), who they are with (e.g., alone, with family), what activity they were doing before the measurement (e.g., studying, working), and how they rate that activity on a scale from very unpleasant to very pleasant. In subsequent EMA assessments after the first one of the day, participants are asked if they performed a suggested activity (yes/no). If they answer no, they are asked for the reason (e.g., did not feel like it, did not have energy, was not convenient, or other). If they answer yes, they rate how pleasant the activity was (very unpleasant to very pleasant) and how much satisfaction it provided (none at all to very much). The evening questionnaire includes additional items: an assessment of overall activity level during the day on a scale from not active at all (1) to very active (7), an evaluation of the best moment of the day on a scale from very unpleasant to very pleasant, and an open field for comments. The evening survey serves as a reflection on the day rather than as a decision point (see procedure). Finally, daily step counts are passively collected once a day via the participants’ smartphone sensors, as higher daily step counts are an indication of improvement in depressive symptoms [28].

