#### Proximal outcomes

The effects of the JITAIs on the proximal outcomes will be analyzed with mixed-effects models. This type of model considers the nested structure of the data (e.g., multiple observations per individual per day) and adequately handles missing data [37]. In our primary analysis, we will examine the average proximal effect of delivering a JITAI (i.e., a message with an activity prompt) versus not delivering a JITAI (i.e., no message) on the depression scores (i.e., tailoring variables; average of the depression items), well-being scores (i.e., average of the two wellbeing items) at the next EMA and the daily step count, across participants and across randomized decision points. In a secondary analysis, we will examine whether the proximal effects of the JITAIs vary with time by examining the linear time trend of delivering a JITAI, assessed by estimating the interaction between the proximal effects of the JITAIs and the study day. Furthermore, moderation analyses will be conducted to evaluate whether the effect of JITAIs on the proximal outcomes depends on contextual factors by calculating the interaction effects between the intervention and contextual factors (i.e., situation: alone, with other people, at home, or outside). Sensitivity analyses will be performed by adding patient sex, age, symptom severity at baseline, and EMA survey depression item scores as covariates to the unadjusted model.

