#### Sample size

The primary feasibility outcome is dose-received adherence, defined as the proportion of completed JITAIs among all received JITAIs during the MRT phase. A sample size calculation for this outcome was based on the precision of the estimated proportion of completed JITAIs among received JITAIs [39]. Because adherence was defined at the JITAI level, with repeated observations nested within participants, the calculation was adjusted for within-participant correlation using a design effect [40]. During the 6-week MRT phase, participants can have up to 168 decision points (42 days × 4 per day). Assuming participants are available at 66% of these moments and a probability of 25% of receiving a JITAI at a given decision point, participants are expected to receive approximately 28 JITAIs on average. Assuming an adherence proportion of 0.60, a two-sided 95% confidence interval, an average of 28 received JITAIs per participant, and a within-participant intraclass correlation of 0.05, 46 participants would yield an approximate confidence interval half-width of 0.041.

We set the recruitment target for the TAU + JITAI group at 52 participants, comprising the 46 participants indicated by the feasibility-based precision estimate plus 6 additional participants to allow for 13% dropout observed in samples with depression [41]. For consistency in the nonrandomized comparison, we will recruit an equal number of participants in the TAU group. The proximal and distal outcome analyses are intended to provide preliminary estimates to inform a future trial.

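### Ranking baseline items by highest average can pick the wrong tailoring item, because 'I feel energetic' runs the opposite way, and the proximal depression score is not defined once

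*Protocol article*

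**What the plan says.** All references are to the Protocol article.

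- **Items (Measures, EMA survey).** "Four items assessing depressive symptoms, which are based on the PHQ-9, are related to mood and energy level". The four are down, tired, listless and energetic. All are rated from 1 (not at all) to 7 (very much), so a high score is a worse state on the first three and a better state on energetic.
- **Eligibility (Procedure, Evaluation phase).** The plan recognises the mixed wording and says that "thresholds are operationalized in a directionally consistent way": at least 4 on the negatively worded items, while for energetic "eligibility is defined as a score ≤ 4".
- **Choice of tailoring items (same section).** The first tailoring variable is "one of the EMA items assessing depressive symptoms that exhibited the highest average score during their baseline period". No recoding is mentioned. For the second, "the participant identifies which symptom most hindered their daily functioning and/or engagement in planned activities", on reviewing the plotted baseline data with a researcher.
- **Outcome (Data analyses, Proximal outcomes).** The depression outcome in the main proximal analysis is given as "depression scores (i.e., tailoring variables; average of the depression items", measured at the next EMA. The text does not say whether energetic is recoded.

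**The concern.** The direction of energetic is handled in one stated rule and not in the next. A ranking by highest average finds the most troublesome symptom only if every item rises with severity, and one of the four does not. The chosen item then helps decide at which moments a participant can be randomised. A wrongly chosen item therefore shapes the data as they are collected and cannot be put right in the analysis.

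The outcome definition raises a related question. Two personal tailoring items and the average of the depression items are different scores. Either could contain energetic, and an unreversed item would pull against the others. The Discussion says the proximal estimates are meant to inform larger trials, so the meaning of this score matters even in a feasibility study.

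**Working it through.** **1. The plan's own figure.** The only design calculation concerns adherence (Sample size): "46 participants would yield an approximate confidence interval half-width of 0.041".

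- JITAIs per participant: 168 × 0.66 × 0.25 = 27.7, about 28.
- Design effect: 1 + (28 − 1) × 0.05 = 2.35.
- Half-width: 1.96 × √[0.6 × 0.4 × 2.35 / (46 × 28)] = 0.041.

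The figure reproduces, and item direction does not enter it.

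**2. Is energetic held as a raw score?** On a 1–7 scale the reversed score is 8 − x. A raw score of 4 or less is the same as a reversed score of 4 or more, since 8 − 4 = 4. Had the item already been reversed, one threshold of at least 4 would have served all items. A separate threshold makes sense only if the item is raw when the threshold is applied. The ranking rule comes next in the text and states no change.

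**3. When do the two rankings differ?** Let M be the highest baseline mean among down, tired and listless, and e the mean of energetic. Ignoring ties:

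- the literal rule picks energetic when e > M;
- an aligned rule picks it when 8 − e > M, that is, e < 8 − M.

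The documents give no item means, so these cases are illustrative:

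| down / tired / listless / energetic | M | 8 − M | Energetic reversed | Literal pick | Aligned pick |
|---|---|---|---|---|---|
| 4.0 / 4.2 / 4.1 / 5.0 | 4.2 | 3.8 | 3.0 (least symptomatic) | energetic | tired |
| 5.0 / 5.5 / 5.2 / 2.0 | 5.5 | 2.5 | 6.0 (most symptomatic) | tired | energetic |
| 3.5 / 3.6 / 3.4 / 4.2 | 3.6 | 4.4 | 3.8 (most symptomatic) | energetic | energetic |

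The first row chooses an item because the participant is doing well on it. The second misses the worst symptom. In the third the literal rule is right. If M is above 4, then 8 − M is below M and the two rules can never both pick energetic; if M is below 4 they can.

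**4. How often?** This cannot be derived from the documents. A simulation assumed equal aligned means of 4 to 5 on the four items, between-person SD of 1 to 1.3 and inter-item correlation of 0.3 to 0.7. The literal rule picked energetic in 4% to 40% of participants, and energetic was the least symptomatic item in 31% to 56% of those. Energetic was the worst item but was missed in 16% to 24% of all participants. The width of these ranges shows how far they depend on the assumptions.

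**5. The outcome, if energetic were not reversed.** Suppose a JITAI lowers down, tired and listless by d each and raises energetic by kd.

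- Four-item mean, reversed: change of −(3 + k)d/4.
- Four-item mean, unreversed: change of −(3 − k)d/4.
- Raw ratio: (3 − k)/(3 + k), which is 1.00 at k = 0, 0.71 at k = 0.5, 0.50 at k = 1, 0.20 at k = 2 and 0 at k = 3.

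For the standardised effect, take k = 1, item SDs of 1 and a common correlation r among aligned items. The SD of the reversed mean is √[(1 + 3r)/4]. That of the unreversed mean is √(4/16) = 0.5, because three pairs correlate at +r and three at −r. The ratio of standardised effects is (0.5/0.5) ÷ (1/√[(1 + 3r)/4]) = √[(1 + 3r)/4]: 0.69 at r = 0.3, 0.79 at r = 0.5 and 0.88 at r = 0.7.

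If the outcome is instead the mean of the two personal items and one is unreversed energetic, equal effects give (−d + d)/2 = 0.

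**The case against.** **Silence on recoding is not an error.** The analysis section neither states nor excludes it, reverse scoring is routine detail for a fuller protocol or SAP, and the threshold shows that the mixed wording was noticed. This stands. A reader might infer that the plan averages energetic unreversed and so halves any true effect. The text does not say so, and exact halving also needs a four-item mean, equal effects on all items and raw units.

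**The equation of the two scores may be loose wording.** The EMA survey section describes the mood and energy items together as serving as tailoring variables, and in that wide sense the phrase fits a four-item mean. But the Evaluation phase section gives the term a narrower meaning, two items per participant, so the outcome remains open to two readings.

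**The second tailoring variable is a safeguard.** It does not depend on score direction, so low energy can enter that way. This limits the harm but leaves the first variable uncorrected.

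**Randomisation through energetic still requires a score of 4 or less.** Such moments are low-to-moderate energy states, and the 50:50 within-person allocation is untouched. This also stands. A reader might infer that affected participants would have few eligible decision points, or that the rule never picks energetic when low energy is the main problem. The first needs item distributions that the documents do not give. The third row of the table contradicts the second.

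**Primary outcome.** Feasibility is judged on adherence, and its definition does not use these items.

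**Conclusion.** The concern holds in a limited form. The ranking rule is a stated operational rule that does not fit the item direction acknowledged in the same section. Read literally, it can select a participant's healthiest item and can miss low energy when that is the worst symptom, so eligibility through this variable can rest on the wrong item. This follows from the wording and the 1–7 scale alone. Its frequency is unknown, and the second tailoring variable offsets part of it.

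The outcome point is one of clarity. The depression score has two possible definitions and no stated recoding. Attenuation is conditional on energetic being left unreversed: by half in raw units for a four-item mean with equal effects, and to about 0.69–0.88 of the standardised effect for r of 0.3 to 0.7 under equal item SDs.

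The point is worth settling before tailoring items are chosen, because the choice cannot be undone afterwards. It does not threaten the primary outcome.

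**What to change.** 1. In the Evaluation phase section, state that energetic is recoded as 8 minus the score before baseline averages are ranked. The existing threshold can stay, since a raw score of 4 or less is already equivalent to a recoded score of 4 or more.
2. In the analysis section on proximal outcomes, define the depression outcome once, as the mean of the four items with energetic recoded. Remove the equation with the tailoring variables, or name the two personal items (also aligned) as a separate secondary outcome.

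The cost is a sentence in each section and a check that the ranking procedure in use follows the first. No extra data or participants are needed. For any participant whose items are already set, the same baseline week allows the aligned ranking to be recomputed, so that discrepancies can be counted and reported.

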#### Distal outcomes

For the distal outcomes (PHQ-9, MHC-SF, QPR, and EQ-5D), propensity score matching will be used to match participants in the TAU group with those in the TAU + JITAI group. Propensity scores are calculated via logistic regression analysis [38], which models the probability of receiving treatment (TAU + JITAIs versus TAU) as a function of baseline covariates, including sex, age, and severity of depressive symptoms at the start of treatment. After the propensity scores are calculated, participants from the TAU group are matched with participants from the TAU + JITAIs group via a matching method (nearest neighbor matching with a caliper). This method ensures that each participant in the TAU + JITAIs group has a corresponding participant in the TAU group with a similar propensity score, making the groups similar in terms of the matched covariates. The matched sample is then used in a mixed-effects model that considers the paired nature of the matched sample by including the matched pairs as random effects. This ensures the correct estimation of standard errors and appropriate interpretation of the results. The fixed effects in the model include time (baseline, 1-week and 6-week assessment), group status (TAU + JITAIs versus TAU), and their interaction, whereas the random effects model includes variability between matched pairs and within individual participants over time. A significant interaction suggests that changes in the outcomes (PHQ-9, MHC-SF, QPR, and EQ-5D) differ between groups.

Participants may pause or discontinue the JITAI component at their own request, at the advice of the treating clinician. Data collected until then will be used for analyses, and participants will be asked to complete the outcome questionnaires. This will not affect access to TAU, and no protocol-driven modification of TAU is planned. Possible harms are expected to be limited and may include burden, annoyance, or temporary distress related to EMA or prompts. Any adverse events will be documented and discussed with the treating clinician.

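### Only the TAU + JITAI group is paid for completing the last questionnaires, so the incentive to supply the distal outcomes differs between the groups being compared

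*Protocol article*

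**What the plan says.** Protocol article, Procedure, Evaluation phase: the four distal questionnaires are given at baseline, at the start of the JITAI phase and at the end of treatment. For the comparator, "Participants in the TAU group will complete these questionnaires (PHQ-9, MHC-SF, QPR, EQ-5D) at the same time points". The payment rule follows directly: patients "in the TAU + JITAI group will receive a remuneration of 25 euros when they have completed the questionnaires at the last time point". The only other patient payment in the article belongs to the design phase: "Patients will receive a remuneration of 25 euros after completing the focus group interviews".

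The same section states that "Allocation to the TAU + JITAI and TAU groups is not randomized" and that "participants, therapists, and researchers are not blinded to study condition".

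Data analyses, Distal outcomes: propensity scores are built from "baseline covariates, including sex, age, and severity of depressive symptoms at the start of treatment". The matched sample then enters a mixed-effects model with fixed effects for "time (baseline, 1-week and 6-week assessment), group status (TAU + JITAIs versus TAU), and their interaction". The interaction is the test of a group difference in change.

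Sample size: 46 participants from the feasibility precision calculation plus 6 for 13% dropout give 52 for TAU + JITAI. For the comparator, "we will recruit an equal number of participants in the TAU group", for the sake of consistency. No retention rate for TAU is given. The section calls the proximal and distal results preliminary estimates for a future trial.

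**The concern.** The 25 euros depends on completing the last assessment, which contains the four instruments compared between groups. One group is paid to supply those scores; the other does the same task unpaid. Group membership may therefore influence who is observed at the time point that carries most of the information on change.

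The planned methods give only partial protection. Matching balances characteristics measured before the incentive acts. The mixed model tolerates final-wave loss that earlier observed scores explain. It does not correct loss that depends on the unobserved final score, for example patients who feel worse, or who have recovered and lost interest. Only two earlier waves are available to predict the final one, and they are about a week apart. The Discussion warns of limited sample size and Type II error for this comparison but does not mention unequal follow-up.

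At stake is the estimate of change versus TAU that is meant to inform a later trial. A final score that was never collected cannot be recovered in the analysis.

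**Working it through.** **1. The plan's own figures.** With p = 0.60, m = 28 JITAIs per participant, ICC = 0.05 and n = 46:

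- Design effect = 1 + (28 − 1) × 0.05 = 2.35.
- Half-width = 1.96 × √(0.60 × 0.40 × 2.35 / (46 × 28)) = 0.041, as stated.
- Recruitment: 46 + 6 = 52, with 6/46 = 13%. Dividing by the retained fraction, 46/0.87, would give 53, a trivial difference.

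These figures size the feasibility outcome in TAU + JITAI. They contain no assumption about follow-up in TAU, and the present point does not depend on them.

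**2. The passages side by side.**

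| | TAU + JITAI | TAU |
|---|---|---|
| PHQ-9, MHC-SF, QPR, EQ-5D at last time point | yes | yes |
| CSQ-8, SUS, TWEETS at last time point | yes | no |
| EMA surveys through the study | yes | no |
| 25 euros on completing the last questionnaires | yes | none stated |

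The asymmetry in payment is a stated rule, and it covers forms that both groups complete.

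**3. Illustration of size.** Only the 13% and the 52 per group come from the protocol; every other input is assumed. Let d be the final-wave loss in a group, and δ the non-responder minus responder difference in outcome, in SD units, taken as equal in both groups. The full-group mean is the responder mean plus d × δ. A completer-only contrast is therefore shifted by (d_TAU − d_JITAI) × δ in absolute terms. Final scores per group are 52 × (1 − d).

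| Loss TAU + JITAI | Loss TAU | Final scores (TAU + JITAI / TAU) | Shift, δ = 0.5 | Shift, δ = 1.0 |
|---|---|---|---|---|
| 13% | 13% | 45.2 / 45.2 | 0 | 0 |
| 13% | 20% | 45.2 / 41.6 | 0.035 | 0.07 |
| 13% | 30% | 45.2 / 36.4 | 0.085 | 0.17 |
| 20% | 13% | 41.6 / 45.2 | −0.035 | −0.07 |

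The sign depends on which group loses more. It would also flip if non-responders did better rather than worse than responders.

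**4. Precision.** For a simple completer comparison that ignores pairing, repeated measures and any caliper losses, the difference detectable with 80% power (two-sided 5%) is 2.80 × √(1/n₁ + 1/n₂). That is 0.589 SD with 45.2 versus 45.2 final scores and 0.624 SD with 45.2 versus 36.4. The loss of precision is small, so selective loss is the larger worry.

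**5. Effect of the planned model.** The shifts in step 3 are for completers only. The planned model uses all three waves, so a participant who misses only the last one still contributes. Where loss follows earlier scores, the bias would be smaller than shown. Where it depends on the unseen final score, bias remains.

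**The case against.** The strongest defence is that the payment is ordinary compensation for a much heavier task. TAU + JITAI patients complete a baseline diary week, then 42 days with four decision-point surveys and an evening survey each day. Their final forms also include the three acceptance questionnaires, which exist in that group only and are secondary outcomes. The payment protects those data. This explains why the group is paid. It does not explain why the comparator receives nothing for the forms both groups complete.

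A reader might infer that the rule must produce lower response in TAU and so bias the comparison in a known direction, for instance by 0.2 to 1.0 PHQ-9 points (0.10 × 2 to 0.20 × 5: assumed excess TAU loss times an assumed difference in change). The protocol does not support that. It gives no retention by group. The diary burden could raise loss in TAU + JITAI, in which case the payment might narrow a gap. The calculation is also completer-only and ignores the planned mixed model.

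A reader might also infer that the 13% allowance was assumed for both groups. The Sample size section applies it to TAU + JITAI and merely sets TAU to an equal number.

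It also stands that the comparison is nonrandomised, unblinded and labelled preliminary, so it could not carry a firm causal claim even with equal payment.

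**Conclusion.** The point holds as a differential incentive with a risk of unequal, possibly informative missingness at the last assessment. Its direction and size cannot be determined from the protocol. Under the assumptions shown, the completer-only shift runs from −0.07 through 0 to 0.17 SD, and the mixed model would reduce it where loss follows observed scores.

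The effect is confined to the distal comparison. Dose-received adherence is measured within TAU + JITAI, acceptance is collected only there, and the micro-randomised contrast is within participants, so none of these is affected. Severity is minor to moderate. It merits action mainly because the remedy is cheap and must be in place before the final data are collected.

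**What to change.** - Offer TAU participants the same 25 euros for completing the shared last-wave questionnaires. The cost is at most 52 × 25 = 1,300 euros plus an amendment, for which the Protocol amendments section already provides a route.
- If extra compensation for EMA burden is wanted in TAU + JITAI, describe and pay it separately from the payment for the shared questionnaires.
- Report final-wave completion of the four distal questionnaires by group. This adds no data collection.

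Making the TAU + JITAI payment unconditional on the final forms would also remove the asymmetry, but it is not recommended. It would take away the incentive for the acceptance questionnaires, and for the final questionnaires of those who stop the JITAI component, who are still asked to complete the outcome measures.
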